## Abstract

**Background:**

Of all workers in Dutch construction industry, 20% has an elevated risk of cardiovascular disease (CVD). A major risk factor for CVD risk is an unhealthy lifestyle. The aim of our study is to design a lifestyle intervention for construction workers with an elevated CVD risk, and to evaluate its (cost-) effectiveness.

**Methods/Design:**

In a RCT, 692 participants will be randomised to either the control or the intervention group. The control group will receive usual care. For the intervention group, a lifestyle intervention has been designed based on interviews and current literature. The intervention will last 6 months and will comprise 3 face-to-face and 4 telephone contacts, consisting of individual counselling aimed at increasing daily physical activity (PA) and improving dietary behaviour, and/or smoking cessation. Counselling will take place at the Occupational Health Service (OHS), and will be done according to motivational interviewing (MI). Additional written information about healthy lifestyle will also be provided to those in the intervention group. At baseline, after 6 and after 12 months, measurements will take place. Primary outcome variables will be the lifestyle behaviours of concern, i.e. daily PA, dietary intake, and smoking status. Secondary outcome variables will be body mass index (BMI), systolic and diastolic blood pressure, total and HDL blood cholesterol, Hba1c and cardio-respiratory fitness (CRF). Sickness absenteeism and cost-effectiveness will be assessed as well. Multilevel analysis will be performed to compare all outcome measures between the intervention group and the control group.

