
## Methods/Design

### Study design

In this randomised controlled trial (RCT) we aim to include 692 workers with an elevated CVD risk. The intervention will consist of individually-based lifestyle counselling, plus short written materials about CVD and healthy lifestyle. The control group will receive care as usual. Measurements will take place at baseline, after 6 and after 12 months. The study protocol was approved by the Ethics Committee of the VU University Medical Centre.

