### Randomisation and stratification

After baseline measurements, all participants will be randomly assigned to the intervention or the control group. The study population will be pre-stratified by type of work (blue collar or white collar). Randomisation will take place at the individual level. Using Random Allocation Software (Version 1.0, May 2004, Isfahan University of Medical Sciences, Iran) a random list of letters A and B will be generated for both strata. A research assistant will assign a letter to each of the two groups.

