### Sample size calculation

The sample size is based on detecting a difference in daily PA according to the guideline for moderate intensity PA. Previous PHSs (2005) showed that 38% of construction workers with an elevated CVD risk was physically inactive according to this guideline. To show a 10% difference between the intervention and the control group after 26 weeks, i.e. 38% inactivity in the control group and 28% inactivity in the intervention group, with a power of 80% and a 95% confidence interval (α = 0.05), 692 persons will be needed (346 in each group). As we expect a loss to follow-up of 20%, 866 persons will be included at baseline. Based on an assumed initial non-response of 50%, we will invite 1,732 workers. In The Netherlands, each month approximately 3,334 workers are screened in a PHS. Based on PHS data obtained in 2006, we expect that on average approximately 667 of them (20%) will fulfil the inclusion criteria. Therefore, we expect that the recruitment period will last at least 3 months. The numbers are presented in Figure 1.

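### The Abstract and Study design section give 692 as the number randomised or included, but the sample size section needs 692 after loss to follow-up and plans 866 at baseline

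*Protocol article*

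**What the plan says.** The protocol article states its size in three places.

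- Abstract, Methods/Design: "In a RCT, 692 participants will be randomised to either the control or the intervention group".
- Study design: "In this randomised controlled trial (RCT) we aim to include 692 workers with an elevated CVD risk".
- Sample size calculation: for "38% inactivity in the control group and 28% inactivity in the intervention group", "692 persons will be needed (346 in each group"). The same section continues: "As we expect a loss to follow-up of 20%, 866 persons will be included at baseline". It then doubles 866 to 1,732 invitations, to allow for 50% non-response.

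The Randomisation and stratification section links the baseline count to the number randomised: "After baseline measurements, all participants will be randomly assigned to the intervention or the control group".

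**The concern.** In the Sample size calculation section, 692 is the number required before the allowance for loss, that is, the number who should still provide data at 26 weeks. The Abstract attaches the same figure to randomisation. The Study design section attaches it to inclusion, which is the term that the sample size section uses for 866. Both figures cannot be the number entering the trial.

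The number randomised is a figure that readers take from an abstract and later compare with the flow of participants in the results paper. Measured against 692, a trial that entered 692 men would seem to have met its target, although the sample size section would count it as 174 short. If anyone ran recruitment to the smaller figure, the allowance for loss would disappear and power would fall below the stated 80%.

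**Working it through.** **Inputs, all from the Sample size calculation section unless noted.** Inactivity at 26 weeks is p1 = 0.38 (control) and p2 = 0.28 (intervention), so the difference is 0.10 and the mean is 0.33. Power is 80% and α is 0.05. Two-sided testing is not stated in words. It is inferred from the 95% confidence interval and supported by the match in step 1. Loss is 20%, non-response is 50%, and groups are equal. That everyone is randomised after baseline comes from Randomisation and stratification.

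**Step 1: the number needed.** Two proportions, pooled variance under the null, no continuity correction:

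n per group = [1.960 × √(2 × 0.33 × 0.67) + 0.8416 × √(0.38 × 0.62 + 0.28 × 0.72)]² / 0.10²

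= [1.960 × 0.6650 + 0.8416 × 0.6612]² / 0.01 = (1.3033 + 0.5565)² / 0.01 = 345.9, rounded up to 346.

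Two groups give 692, which matches the plan exactly. Other versions of the formula do not match: 344 per group unpooled, 366 with continuity correction, 273 one-sided.

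**Step 2: the allowance for loss.** 346 / 0.8 = 432.5, rounded up to 433 per group, or 866 in total. This also matches exactly. In reverse, 866 × 0.8 = 692.8. So within this section 692 is the number after loss and 866 the number before it.

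**Step 3: invitations.** 866 / 0.5 = 1,732, as stated. At about 667 eligible men a month, 1,732 / 667 = 2.6 months, in line with a recruitment period of at least three months. Recruitment is therefore planned around 866.

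**Step 4: can the two figures be reconciled?** That would need some step between baseline and randomisation that removes 174 men. There is none. Everyone is randomised after baseline, and the sample size section attributes the gap between 866 and 692 only to loss to follow-up.

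**Step 5: power under each figure.** Power = Φ{[0.10 × √n − 1.3033] / 0.6612}, where n is the number per group with data.

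| Randomised | Left after 20% loss | Per group | Power |
|---|---|---|---|
| 866 | about 693 | 346 | Φ(0.842) = 80.0% |
| 692 | about 554 | 277 | Φ(0.546) = 70.7% |

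For the second row, the unpooled version gives 71.1% and the continuity-corrected version about 67.5%.

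**The case against.** The strongest defence is that the operative section is right. The number is derived only in the Sample size calculation section, every step there reproduces, and the invitations follow from 866. The Abstract and Study design section are summaries, and most probably the calculated figure was carried into them without the allowance for loss. The recruitment figure in the article is not shown in the text at hand and may already display 866. All of this stands. It makes the point a correction of wording and not a flaw in the design.

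A reader might infer from the Abstract that the trial is planned with only about 71% power, or that the sample size arithmetic is wrong. The documents support neither. No calculation is in error, and no passage describes stopping recruitment at 692. The 174 men are a gap between two statements, not a shortfall in planned recruitment.

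The 71% also has limits of its own. It describes an unadjusted comparison of two proportions in which men lost to follow-up contribute nothing. The Data analysis section plans regression adjusted for the baseline value, so the figure belongs to the planning formula and not to the planned analysis.

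The defence does not remove the contradiction. A condensed article may leave details out, but here it makes a positive statement about the number randomised that its own sample size section contradicts. Nor does the intention-to-treat analysis rescue 692 as the number to randomise, because the plan's own increase to 866 assumes that lost men provide no 26-week data.

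**Conclusion.** The point holds as an internal inconsistency in the stated sample size. Two of the three statements of trial size give the number needed after loss as the number entering the trial; the number that the plan intends to randomise is 866. The difference is 174 men, or 174/866 = 20% of the intended number.

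The calculation is correct, and 866 randomised delivers 80% power under its own assumptions. A fall to about 71% is strictly conditional. It would arise only if recruitment actually stopped at 692, and it rests on 38% against 28% inactivity, two-sided α of 0.05, 20% loss, and no data from those lost. The point is worth correcting because the number randomised is a core design figure and the correction costs almost nothing, but it is not evidence of an underpowered design.

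**What to change.** In the Abstract and in the Study design section, replace 692 with a statement that 866 men (433 per group) will be randomised, to yield about 692 evaluable at 26 weeks. The Sample size calculation section needs no change. The recruitment figure should be checked to show 866 at the point of inclusion.

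The cost is two sentences. The plan already provides for 866 men at baseline and 1,732 invitations, so neither resources nor analysis change. If, against the rest of the article, 692 really were the number to be randomised, the sample size section would have to be rewritten and would have to state the resulting power of about 71% with 20% loss.

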**Discussion:**

By improving lifestyle, CVD risk may be lowered, yielding benefits for both employee and employer. If proven effective, this lifestyle intervention will be implemented on a larger scale within the Occupational Health Services in construction industry.

**Trial registration:**

Current Controlled Trials ISRCTN60545588

## Background

In the Netherlands, cardiovascular diseases (CVD) are responsible for one third of all deaths each year. Besides to premature death and a decreased quality of life, CVD morbidity leads to high costs for health care and loss of productivity [1]. An unhealthy lifestyle, e.g. smoking, unhealthy diet and/or insufficient daily physical activity PA, is a major cause of CVD [2]. Well-known consequences of an unhealthy lifestyle are overweight, an unfavourable total/HDL cholesterol ratio, and an elevated blood pressure [3,4]. Improved lifestyle may contribute to an improved CVD risk profile. As to smoking cessation, it has been shown that those who have quit smoking quickly reduced the risk of CVD [2,5]. As to diet, there are several ways to decrease the CVD risk. For instance, diminishing intake of saturated fat will lower LDL and total cholesterol [2]. A diet low in salt has a beneficial effect on blood pressure [6]. Fruits and vegetables are rich in micronutrients and fibre and therefore protective against CVD [7]. Moreover, obesity, a major CVD risk factor, may be prevented by lowering calorie intake [8]. As to PA, there is sufficient evidence that regular PA is beneficial for health, not only by preventing weight gain but also by improving cardio respiratory fitness (CRF) [9,10]. In 1995, the Centers for Disease Control and Prevention (CDC) and the American College of Sports Medicine (ACSM) achieved consensus about the level of PA needed for good health. This recommendation stated that every adult should accumulate 30 minutes or more of moderate-intensity PA on most, preferably all, days of the week [11]. Next to this Public Health recommendation on moderate PA, the ACSM stated that each adult should perform vigorous exercise for 20 minutes or more, at least 3 times a week in order to improve CRF [12]. Like in the general Dutch population, an unhealthy lifestyle is commonly seen in Dutch construction industry. Even though the percentage of construction workers that fulfilled the guideline for moderate PA in 2005 (61%) was higher than that of the general Dutch male population (51%) [13], the prevalence of overweight and obesity in the construction industry was considerably higher than in the general Dutch population (64% vs. 51% and 15% vs. 10%, respectively). Only 18% of construction workers fulfilled the guideline for vigorous PA, as compared to 25% of the general Dutch male population. Furthermore, one third of all workers in the construction industry are smokers [14]. Since a substantial part of the ageing population in construction industry has an unhealthy lifestyle, CVD morbidity and mortality in this population is likely to rise in the following years. Sickness absenteeism due to CVD and other chronic diseases may also increase. In collaboration with Arbouw, a national organisation involved in monitoring and improving working conditions and occupational health of workers in construction industry, we will investigate the effectiveness and cost-effectiveness of an individual lifestyle intervention for male construction workers at risk for CVD. The aim of the intervention is to lower the risk for CVD by changing one or more lifestyle behaviours. As the intervention will be focussed on improving three lifestyle topics, i.e. diet, PA, and smoking, we hypothesise that in the intervention group diet will be improved, the amount of PA will be increased, and the number of smokers will be lowered. As these lifestyle components are important CVD risk factors, we further hypothesise that mean BMI, blood pressure, HbA1c and total cholesterol will be lowered and HDL cholesterol will be increased as a result of the intervention. In this article we will describe the design of this study, which has been named 'Health under Construction'.

## Methods/Design

### Study design

In this randomised controlled trial (RCT) we aim to include 692 workers with an elevated CVD risk. The intervention will consist of individually-based lifestyle counselling, plus short written materials about CVD and healthy lifestyle. The control group will receive care as usual. Measurements will take place at baseline, after 6 and after 12 months. The study protocol was approved by the Ethics Committee of the VU University Medical Centre.

### Setting

The study population will be recruited from all Occupational Health Services (OHSs) throughout The Netherlands that perform Periodical Health Screenings (PHSs) in construction industry. A PHS is offered every four years to all construction workers under the age of 40. Workers above the age of 40 are invited for a PHS every two years. All occupational physicians (OPs) and occupational nurses employed at the abovementioned OHSs were invited to apply for the role of lifestyle counsellor in our study. We made a selection based on their motivation, interest in lifestyle, and affinity with the target group.

### Study population

The study population exists of workers in Dutch construction industry who have an elevated risk of CVD. Since less than 10% of workers in construction industry is female, we decided to include only men. Two types of construction workers can be distinguished. More than 75% of all workers take part in the actual construction process ('blue collar workers') and the remaining are mainly involved in planning, supervision en administration ('white collar workers'). Both blue and white collar workers will be included in the study. Their CVD risk will be derived from their PHS results. The PHS consists of a questionnaire to be filled in by the worker at home, and a physical examination, which is performed by an OP or an occupational nurse at the OHS. In the PHS, both work-related health and lifestyle-related health, e.g. smoking, body mass index (BMI), and cholesterol are assessed. Until recently, there was no instrument for determining the workers' risk of CVD based on all risk factors measured in the PHS. For the purpose of this study, we developed such a risk assessment instrument. For this instrument, we used the scores for age, total and HDL cholesterol, blood pressure and smoking, as determined in the Framingham risk score. The Framingham risk score is a widely used sensitive screening instrument for predicting the 10-year risk of coronary heart disease, and is applicable to the US as well as to European populations [15]. Our risk assessment instrument differs from the Framingham risk score because of a lack of data on diabetes. Besides, the risk assessment instrument was elaborated by six additional CVD risk factors, i.e. BMI, alcohol intake, HbA1c, psychological complaints, heart complaints and the amount of weekly PA, measured in the PHS for Dutch construction workers. The cut-offs for these additional CVD risk factors were defined based on expert consensus, recent research and general Dutch standards [16,17]. In Table 1, all inclusion criteria are presented. Of all blue and white-collar workers in Dutch construction industry who will be subject to a PHS between January 2007 and October 2007, those meeting the inclusion criteria will be invited to participate. The invitation letter will be accompanied by a brochure with background information about the study, an informed consent form and a questionnaire. Those who agree to participate, by signing and sending back the informed consent form and the questionnaire, will be included in the study. Exclusion criteria will be 'inability to be physically active', and 'not sufficiently capable of using the Dutch language'.

**Table 1 T1:** Inclusion criteria for the study population.

**Variable**	**Criteria**
Gender	Male
Age	18–65 years
Permission	Signed informed consent
Availability	Available for the study for 12 months following inclusion.
Health status	Having a 10-year risk of coronary heart disease higher than average compared to the same age group according to the Framingham risk score, *and *having *one or more *of the following risk factors:
	• Insufficiently active: Fulfilling none of the Public Health PA guidelines
	• Excessive alcohol use: ≥ 35 glasses of alcohol per week
	• HbA1c ≥ 6.5%
	• Obesity: BMI ≥ 30 kg/m^2^
	• Psychological complaints: Tiredness or stress and/or treated for psychological disorders and/or low motivation to recover from work.
	• Heart-related complaints: Shortness of breath and/or suffering from chest pain and/or diagnosed with or treated for CVD or its predictors, e.g. high blood pressure.

### Randomisation and stratification

After baseline measurements, all participants will be randomly assigned to the intervention or the control group. The study population will be pre-stratified by type of work (blue collar or white collar). Randomisation will take place at the individual level. Using Random Allocation Software (Version 1.0, May 2004, Isfahan University of Medical Sciences, Iran) a random list of letters A and B will be generated for both strata. A research assistant will assign a letter to each of the two groups.

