### Development of the intervention

#### Interviews

Preceding the study, interviews were held with 14 employees, 6 employers and 9 OPs [18]. The aim of those interviews was to get insight in the workers' current lifestyle, their attitudes towards changing behaviour, their preferences for the type of lifestyle intervention and the feasibility of a lifestyle intervention in construction industry. It appeared that white-collar workers in particular reported a lack of regular PA. Most blue-collar workers said to have daily PA at work. However, hardly any of the interviewed workers reported participating in organised sports. In general, the workers thought to have a healthy diet, but some reported to eat large amounts. Most workers had a positive attitude towards a lifestyle intervention, under the condition that participation in the intervention would be voluntary. Most workers said they would prefer at least one face-to-face contact, preferably at the start of the intervention, with a professional health counsellor. As to the frequency of the contacts, most workers suggested about once a month. They were generally positive about additional counselling by telephone. The majority of the workers interviewed thought that brochures about lifestyle would be helpful, if provided additionally. Furthermore, toolbox meetings at work were suggested as a good opportunity for giving lifestyle advice. Email or SMS were not considered as appropriate media. Some of the workers said that they would appreciate involvement of their wives in the intervention, especially if the intervention would focus on a change in dietary behaviour. The 6 employers who were interviewed emphasised that the intervention should not be pedantic, and that the worker should be confronted with his risk profile and the associated negative health consequences. Moreover, the employers agreed that the person carrying out the intervention should be experienced in counselling and he/she should have experience with the target population. From the interviews with the OPs, it was confirmed that there is neither consensus nor a guideline for lifestyle-related health promotion aimed at workers in the construction industry. All of them were enthusiastic about the initiative of developing a lifestyle intervention. To date, OPs hardly perform lifestyle counselling, because of a lack of time, knowledge, and possibilities for follow-up. They suggested linking the lifestyle intervention to the PHS. According to the OPs, the workers' CVD risk should be communicated in a way that is easy to understand, e.g. visually.

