### Primary outcome measures

#### Physical activity

The main outcome measure for PA is whether the participant has started to fulfil one or both of the Public Health recommendations for PA. If so, he is considered to have changed from physically inactive to physically active.

On the PHS questionnaire, he will fill in how many days per week he usually is moderately physically active for more than 30 minutes. From this item, fulfilling the Public Health recommendation for moderate PA can be determined. Furthermore, he will be asked how many days during the last month he has performed vigorous physical activities that lasted long enough to make him sweat. By this item, fulfilling the Public Health recommendation for vigorous PA can be computed. Another outcome measure for PA is the frequency, duration and intensity of PA in leisure time. This will be assessed using the Short QUestionnaire to ASsess Health enhancing physical activity (SQUASH), which was shown to be a fairly reliable and valid questionnaire (*r*_*Spearman *_0.58 and *r*_*Spearman *_0.45 respectively) [44]. The SQUASH was designed to measure four clusters of PA, i.e. commuting activities, household activities, activities at work and school, and leisure time activities. For the purpose of this study, only commuting activities and leisure time activities, i.e. walking, cycling, gardening, odd jobs and sports will be measured, as these activities are considered relevant for the target group. The participant will be asked to fill in how many days per week and how many minutes per day he usually spends on these physical activities, during a usual week within the past month. The level of exertion for each type of activity will have to be indicated as well. The level of exertion for sports, gardening and odd jobs is classified as light, intermediate, and vigorous. The level of exertion for walking and cycling is classified as slow, intermediate, and fast. From the SQUASH, metabolic equivalents (METs) can be estimated. Light activities are rated as 2.0 to < 4.0 METs, moderate activities are rated as ≥ 4.0 to <6.5 METs, vigorous activities are rated as ≥ 6.5 METs [44]. The cluster items about household activities will be left out of the SQUASH questionnaire, as we expect these activities not to be major contributors to daily PA in this population of male construction workers. In addition, the SQUASH items about activities at work and school were not considered suitable for our population. The level of exertion, i.e. light, intermediate, or vigorous, of the daily activities at work will be assessed using a single question derived from the TNO questionnaire PA at work [45], which has not been tested for validity and reliability yet.

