### Data analysis

On all outcome measures, intention-to-treat analyses will be performed. Both crude and adjusted linear and logistic regression analyses will be performed. In doing so, analysis for covariance will be conducted adjusting for the outcome variable measured at baseline. In the adjusted model, other potential confounders will be included as covariate, such as age and work activities. Furthermore, effect modification, e.g. by family history, will be checked. First of all, data will be analysed for the whole intervention group, that is, irrespective of the intervention received. Secondly, subgroup analysis will be done among those having received the smoking or the energy balance intervention. As all participants will have to indicate at baseline which lifestyle behaviour they prefer to change, the participants in each intervention subgroup will be compared to those in the control group having indicated the same type of intervention preference. Cost-effectiveness ratios will be calculated by dividing the difference between the mean total costs between the two study groups by the difference in the mean effects. For each outcome measure used in this evaluation, cost-effectiveness ratios will be presented graphically on a cost-effectiveness plane. To calculate the confidence intervals for the ratios, bootstrapping will be done. For all analyses, a significance of 0.05 will be applied. On the process evaluation, qualitative analyses will be performed.

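### The randomisation stratum (blue or white collar) is not prespecified as a term in the outcome models; adding it is a minor, free improvement

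*Protocol article*

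**What the plan says.** **Randomisation and stratification.** "The study population will be pre-stratified by type of work (blue collar or white collar"). Allocation is at the individual level, and "a random list of letters A and B will be generated for both strata". No block size or other restriction within a list is stated.

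**Study population.** The stratum is defined by the worker's role. "More than 75% of all workers take part in the actual construction process ('blue collar workers"); the rest mainly plan, supervise or administer. The split among trial participants is not given.

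**Data analysis.** "Both crude and adjusted linear and logistic regression analyses will be performed". Then "analysis for covariance will be conducted adjusting for the outcome variable measured at baseline", which reads as applying to both kinds of model. Finally, "In the adjusted model, other potential confounders will be included as covariate, such as age and work activities". Neither the crude nor the adjusted model is called primary. The Abstract mentions multilevel analysis, also without naming the stratum.

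**Primary outcome measures, Physical activity.** A separate variable describes work: "The level of exertion, i.e. light, intermediate, or vigorous, of the daily activities at work will be assessed using a single question", which the article says is not yet tested for validity or reliability.

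**Interviews.** "It appeared that white-collar workers in particular reported a lack of regular PA", while most blue-collar workers said they were physically active every day at work.

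**The concern.** When allocation is stratified, the matching analysis includes the stratum. If the strata are balanced by design and prognostic, a model without the stratum counts between-stratum variation as noise, although the design has already removed that variation from the treatment comparison. Some of the precision that stratification was meant to buy is then lost.

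Here the article's own interviews suggest that type of work is related to physical activity, the behaviour that sizes the trial. Yet the one covariate that the design fixes in advance is not named among the model terms, while age and *work activities* are offered as examples. Because the list is open, the choice to adjust for the stratum could also be made after the data are seen. What is at stake is a little power and a clear prespecification. Bias and false-positive risk are not at issue.

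**Working it through.** **1. Where the stratum could enter.**

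| Model | Terms stated | Stratum present? |
|---|---|---|
| Crude | treatment, baseline outcome | No |
| Adjusted | the same, plus an open list with age and *work activities* as examples | Only if *work activities* means type of work |

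The article calls the stratum type of work. Its exertion item concerns daily activities at work and has three levels. The wording of the covariate is closer to the latter, but the blue/white-collar split is also defined by what the men do, so the text does not settle it.

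**2. The plan's sample size.** Inputs from Sample size calculation: 38% v 28% inactive, 80% power, α = 0.05, taken as two-sided. With pooled variance,

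n = [1.960·√(2·0.33·0.67) + 0.842·√(0.38·0.62 + 0.28·0.72)]² / 0.10² = (1.303 + 0.556)² / 0.01 ≈ 346 per group, 692 in all.

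This matches the article and does not involve the stratum.

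**3. Risk-difference scale, no baseline covariate.** Assumptions: 75% blue collar, balance within strata, and white-collar men g points more inactive in both arms. The article does not give g.

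- SE without the stratum: √[(0.2356 + 0.2016)/346] = 0.03555.
- SE with it: √[(0.4372 − 2·0.75·0.25·g²)/346].
- Power with the stratum: Φ(0.10/SE_with − 1.96).
- Power without it: Φ[(0.10 − 1.96·SE_without)/SE_with].
- Type I error without it: 2[1 − Φ(1.96·SE_without/SE_with)].

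| Gap g | SE with | SE ratio | Power without | Power with | Type I error without |
|---|---|---|---|---|---|
| 0 | 0.03555 | 1.000 | 80.3% | 80.3% | 5.0% |
| 10 points | 0.03539 | 1.004 | 80.4% | 80.7% | 4.9% |
| 20 points | 0.03493 | 1.018 | 80.7% | 81.7% | 4.6% |
| 30 points | 0.03415 | 1.041 | 81.3% | 83.4% | 4.1% |

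So without a baseline term the loss is about 0.2, 0.9 and 2.1 points of power for gaps of 10, 20 and 30 points. At 85% blue collar, the 30-point gap gives a ratio of 1.027 and 81.0% v 82.4%. For a continuous outcome the ratio is 1/√(1 − R²), where R² is the share of variance due to the stratum: 1.005, 1.010 and 1.026 for 1%, 2% and 5%.

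**4. Logistic scale, no baseline covariate, same assumptions.**

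| Gap g | log-OR without (SE) | log-OR with (SE) | z without, absolute | z with, absolute |
|---|---|---|---|---|
| 10 points | −0.455 (0.163) | −0.458 (0.164) | 2.79 | 2.80 |
| 20 points | −0.455 (0.163) | −0.469 (0.166) | 2.79 | 2.83 |
| 30 points | −0.455 (0.163) | −0.490 (0.170) | 2.79 | 2.89 |

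Omission does not widen the standard error here; it is slightly smaller. The estimate moves toward zero, and the net result is again a small loss of power.

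**5. With the baseline outcome in the model, as planned.** Simulated trials with 75% blue collar, balanced strata and gaps of 10 to 30 points; the latent correlation between baseline and follow-up is an assumption.

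- Correlation 0.3 or 0.5: adding the stratum gained about 0.1 to 1.1 points of power in one set (1,500 trials per setting) and about 0 to 1.3 in another. Type I error without the stratum was about 4.1 to 5.4% in the latter.
- Correlation 0.6 or 0.75 (4,000 trials per setting): power without v with the stratum was 86.6 v 86.7% and 91.4 v 91.5% at 10 points, 87.0 v 87.5% and 91.5 v 92.0% at 20, and 85.5 v 86.6% and 92.1 v 92.5% at 30. Type I error without the stratum was 4.6 to 5.6%.

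With 1,500 trials the simulation error of a 5% rate is √(0.05·0.95/1500) = 0.56 points, so these rates show no clear departure from 5%. Baseline activity already carries much of what the stratum would add.

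**6. Dependence on balance.** With unrestricted 1:1 assignment and a 30-point gap, simulated type I error was 5.2 to 5.4% with or without the stratum. The conservatism in step 3 needs balanced lists, which the article does not state.

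**The case against.** The strongest reply is that a condensed article need not print a full covariate list, that *work activities* may well be the stratum, and that about one point of power is not worth a finding. Much of this stands. Nothing in the Data analysis section is false, and the evidence that the stratum is prognostic is thin: interviews with 14 employees, with no figure for the gap. If *work activities* means exertion at work, the adjusted model would still hold a related variable.

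The reply does not remove the point. The article does state its model terms, and on the natural reading the crude models omit the stratum whatever *work activities* means. In the adjusted models it is at best one example in an open list.

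Four stronger readings are tempting, and the document does not support them:

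- *The analysis discards the stratification.* The covariate wording may mean the stratum, so omission from the adjusted models is not shown.
- *All standard errors are too wide.* This fits linear and risk-difference analyses. In the logistic models planned for binary outcomes the odds ratio shrinks toward 1 instead.
- *The test is conservative.* This needs balance within strata, and it largely disappears once baseline is in the model.
- *The omission is worth up to some 53 men.* That figure uses the variance share at a 30-point gap, 0.25·0.75·0.3²/(0.38·0.62) = 7.2%, and 692·[1/(1 − 0.0716) − 1] ≈ 53. It leaves out the baseline covariate that the plan includes.

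**Conclusion.** The point holds as a minor one. Type of work governs allocation but is not fixed as a term in the outcome models, and the phrase that might cover it is undefined. Under the planned baseline adjustment the cost is about 1 point of power or less (simulated range 0 to 1.3). If the crude model were meant to have no baseline term, the risk-difference calculation puts it at about 2 points for a 30-point gap. Type I error is not inflated in any material way, no bias arises, and 692 stands.

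These sizes rest on assumptions that the article does not supply: the inactivity gap (10 to 30 points), 75% blue collar among participants, balance within strata, and the baseline to follow-up correlation. A smaller gap, a higher blue-collar share, or unrestricted lists would make the gain smaller still.

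**What to change.** State in Data analysis that every between-group model, crude and adjusted, linear and logistic, includes type of work (blue or white collar, as used for randomisation) as a fixed covariate next to the baseline outcome. Say what *work activities* means; if it is the exertion item, list it as a separate covariate for the adjusted model.

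The cost is one or two sentences and one degree of freedom per model. The stratum must be known for every man before he is randomised, so no new data are needed and the sample size does not change.
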